### Sample size

The target sample size of 216 (72 from each of the three sites) was derived from the Mental Component Summary (MCS) score of the VR-12 [51], which assumes a power of 80%, alpha of 0.05, mean MCS score difference of 6.5, standard deviation of 15.0 and 20% attrition, reported in the feasibility study [18].

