#### Effectiveness measures and data sources

The effectiveness of the CAST intervention on older adults and their caregivers will be evaluated using a range of patient and caregiver-relevant measures. A summary of these measures, including their description, related variables/outcomes, and time point(s) collected, and methods of analysis, are summarized in Table 1.

**Table 1 Tab1:** CAST Study Outcome Measures Summary

Outcome	Measure	Group*	Timepoint	Method of Analysis
Mental functioning	Mental Component Score of VR-12 (MCS) [51, 55]	PT, CG	T_1_, T_2_, and T_3_	-Descriptive analyses -T1-T2 (Treatment Effect): ANCOVA, complete case and multiple imputation analyses, subgroup analyses, quantile regression -T2-T3 (Sustainability): ANCOVA, complete case and multiple imputation analyses, subgroup analyses
Physical functioning	Physical Component Score (PCS) of VR-12 [51, 55]	PT, CG	T_1_, T_2_, and T_3_	-Descriptive analyses -T1-T2 (Treatment Effect): ANCOVA, complete case and multiple imputation analyses, subgroup analyses, quantile regression -T2-T3 (Sustainability): ANCOVA, complete case and multiple imputation analyses, subgroup analyses
Depressive symptoms	CESD-10 [56]	PT, CG	T_1_, T_2_, and T_3_	-Descriptive analyses -T1-T2 (Treatment Effect): ANCOVA, complete case and multiple imputation analyses, quantile regression -T2-T3 (Sustainability): ANCOVA, complete case and multiple imputation analyses
Anxiety symptoms	Generalized Anxiety Disorder scale (GAD-7) [57]	PT, CG	T_1_, T_2_, and T_3_	-Descriptive analyses -T1-T2 (Treatment Effect): ANCOVA, complete case and multiple imputation analyses, quantile regression -T2-T3 (Sustainability): ANCOVA, complete case and multiple imputation analyses
Perceived social support	Personal Resource Questionnaire (PRQ-2000) [58]	PT	T_1_, T_2_, and T_3_	-Descriptive analyses -T1-T2 (Treatment Effect): ANCOVA, complete case and multiple imputation analyses, quantile regression -T2-T3 (Sustainability): ANCOVA, complete case and multiple imputation analyses
Communication between patients and providers	Patient-Provider Communication questionnaire [59]	PT, CG	T_1_ and T_2_	-Descriptive analyses -T1: z test of proportions for group comparison, complete case analysis -T2: z test of proportions for group comparison, complete case analysis

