#### Analysis: effectiveness evaluation

Descriptive statistics will be used to summarize outcome values at baseline, 6 months and 12 months. Means and standard deviations will be used for continuous outcomes, and frequency and percentages will be used for categorical outcomes. Intention-to-treat analyses using analysis of covariance (ANCOVA) will be used to assess group differences in continuous outcomes from baseline to T2 in order to determine if the intervention was effective over the intervention period. The outcomes include: PRQ-2000, CESD-10, GAD-7, VR-12 PCS, VR-12 MCS, the PPC, CCCQ, and the IC-PREMs. The ANCOVA model will use the 6-month outcome value as the dependent variable, the group indicator as the independent variable and the baseline outcome value as the covariate. Model results will be expressed as mean group differences with accompanying 95% confidence limits. Quantile regression will also be used to examine the treatment effect over a broader range of values (beyond the mean) for the outcome variables. Assessment of group differences in continuous outcomes from T_2_ to T_3_ will be assessed using ANCOVA and will be aimed at assessing the sustainability of the intervention effects (see Table 1).

Z tests of proportions and McNemar tests will be used to assess changes within each group in the number of participants with acute care episodes and the number of acute care episodes from baseline to T_2_, and from T_2_ to T_3_ Acute care episodes include emergency department visits and hospital admissions. Risk difference (intervention risk – control risk) and accompanying 95% confidence limits will be calculated for 6 months for emergency department visits and hospital readmissions for 6 months. As was noted earlier, acute care episodes will be identified using administrative data from IC/ES, and self-reported data from the HSSUI. Due to the highly skewed nature of cost data, a non-parametric test will be used to compare the change in health and social service use and costs from baseline to T_2_ and from T_2_ to T_3_ for the two groups. Outliers are particularly common for certain healthcare costs such as hospital admissions, thus we will conduct a sensitivity analysis to assess the impact of outliers on the cost comparison.

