Subgroup analyses will be conducted for the VR-12 outcomes to determine if the intervention is effective for subgroups of patients from baseline to T2. The following baseline variables have been selected a priori for testing subgroup effects: age, sex, number of chronic conditions, depressive symptoms (CESD-10), site, and dose of the intervention (number of home visits and telephone contacts). Multiple imputation will be used to address missing data. All data analyses will assume a level of significance of 0.05 and be performed using SAS Version 9.4.

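### The subgroup aim asks whether CAST works within each subgroup rather than whether its effect differs between them, and dose is wrongly listed as a baseline subgroup variable

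*Protocol article*

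**What the plan says.** The subgroup paragraph of the protocol article (Analysis: effectiveness evaluation) says that subgroup analyses of the VR-12 outcomes will be done "to determine if the intervention is effective for subgroups of patients from baseline to T2". It continues: "The following baseline variables have been selected a priori for testing subgroup effects: age, sex, number of chronic conditions, depressive symptoms (CESD-10), site, and dose", with dose explained as the number of home visits and telephone contacts. The same paragraph adds: "All data analyses will assume a level of significance of 0.05".

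Only one ANCOVA model is written out. It appears earlier in the section, for the main comparison, with the 6-month value as the dependent variable, "the group indicator as the independent variable and the baseline outcome value as the covariate". No separate subgroup model is given, and no interaction or heterogeneity test is named anywhere in the article.

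The text confines subgroup analyses to baseline to T2. For both the mental and the physical component score, Table 1 also lists "T2-T3 (Sustainability): ANCOVA, complete case and multiple imputation analyses, subgroup analyses".

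The section on implementation outcomes defines dose as the home visits and telephone contacts during the six-month intervention.

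**The concern.** Whether CAST is effective in women, and whether it is effective in men, are two separate tests of the treatment effect. Neither tests whether the effect differs by sex. A significant result in one level beside a non-significant result in the other can easily arise when the effect is the same in both, because each level holds only part of the sample. The trial is sized for the overall comparison on the mental component score alone.

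The aim as worded leads naturally to such within-level tests, each at 0.05. At stake is the reliability of secondary statements that CAST works in some patients or sites and not in others. The primary analysis is not affected.

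Two further points arise in the same paragraph. Dose is called a baseline variable although it does not exist at baseline. The period for subgroup analyses also differs between text and table.

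**Working it through.** **Inputs.** From the Sample size section: "The target sample size of 216 (72 from each of the three sites"; it "assumes a power of 80%, alpha of 0.05, mean MCS score difference of 6.5", with "standard deviation of 15.0 and 20% attrition". Allocation is 1:1 (Randomization and blinding). Assumptions: two-sided testing, which the article does not state; equal halves for binary subgroups, since no cut-points are given; and a baseline-outcome correlation r of 0 to 0.7, which is also not given.

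**The plan's own figure.** Per arm, n = 2 × 15² × (1.960 + 0.842)² / 6.5² = 83.6, so 84. The total is 168, and 168 / 0.80 = 210. With the t distribution it is 85 per arm, 107 after attrition, 214 in total. Both are close to 216, so the sample size reproduces.

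**Overall power.** 216 × 0.80 = 172.8 analysed, or 86.4 per arm. SE = 15 × √(2/86.4) = 2.28. Power = Φ(6.5/2.28 − 1.96) = 81%.

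**Within-subgroup power, same true effect of 6.5 everywhere.**
- Half-sample (43.2 per arm): SE = 15 × √(2/43.2) = 3.23; power = Φ(6.5/3.23 − 1.96) = 52%. The t-based value with 43 per arm is 51%.
- One site (28.8 per arm): SE = 15 × √(2/28.8) = 3.95; power 38%.

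**Disagreement with no true heterogeneity.** The halves contain different patients, so the chance that exactly one is significant is 2p(1 − p). Baseline adjustment reduces the SD to 15 × √(1 − r²).

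| Assumed r | Power per half (normal / t) | Halves disagree (normal / t) |
|---|---|---|
| 0 | 52% / 51% | 50% / 50% |
| 0.5 | 64% / 63% | 46% / 47% |
| 0.7 | 81% / 79% | 31% / 33% |

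For the three sites at r = 0, the chance that they do not all agree is 1 − 0.376³ − 0.624³ = 70%.

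**False positives with no effect.** Binary splits of age, sex, number of conditions and CESD-10 give 8 levels, and three sites make 11. Over two VR-12 outcomes that is 22 tests. Under independence the chance of at least one false positive is 1 − 0.95²² = 68%. The tests share patients, so this is an upper value. A lower value comes from site alone on one outcome, where the groups are disjoint: 1 − 0.95³ = 14%.

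**Interaction test.** For two halves, SE = 15 × √(4/43.2) = 4.56, twice the overall SE. Power for a 6.5-point difference in effect between halves is Φ(6.5/4.56 − 1.96) = 30%, or 37% at r = 0.5. At r = 0 the difference detectable with 80% power is 2.80 × 4.56 = 12.8 points.

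**Dose.** Participants are randomised after baseline data collection, whereas dose counts contacts over the following six months. The coordinator's visits and calls belong to the CAST arm, so usual-care participants have no corresponding value. A group-by-dose term therefore cannot be estimated.

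**The case against.** The strongest objection is that the model without an interaction belongs to the main comparison. The subgroup paragraph gives no model, and its phrase about testing subgroup effects is compatible with an interaction test. A condensed article may leave the form of that test to the analysis plan, which is not at hand. This stands: a reader might infer that the plan specifies a subgroup model with no interaction, but the article does not establish that. What remains is the aim itself, which is stated and poses the wrong question.

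A reader might also infer that chance differences will be reported as real. The article draws no such conclusion and does not describe comparing p-values between levels. Nor does it support the inference that subgroup claims would feed the scale-up plan: Table 2 and the section on sustainability and scale-up list meeting notes, interviews, advisory-board notes and focus groups, and a Citizen Panel, analysed qualitatively.

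The figures rest on assumed equal halves and 11 levels, and the 68% on independence. That is fair, so they are given as conditional figures with ranges. The variables were chosen in advance, which is a strength, but it does not turn within-level tests into a test of difference.

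**Conclusion.** The concern holds as one about the stated aim, not about a proven choice of model. The article asks whether CAST is effective within subgroups, at 0.05, and names no test of whether the effect differs. If that aim is followed by within-subgroup tests, two equal halves with an identical 6.5-point effect would disagree on significance in about 50% of trials with no gain from baseline adjustment, about 47% at r = 0.5 and about 31% at r = 0.7. With no effect, the chance of at least one false positive is at most about 68% over 22 tests, given the assumed splits.

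Two points need no assumption. Dose is not a baseline variable, and the text and Table 1 disagree on whether subgroup analyses extend to T2-T3. The change should be made, but the main effectiveness result does not depend on it.

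**What to change.** - Reword the subgroup aim to ask whether the effect of CAST on the VR-12 outcomes differs by age, sex, number of chronic conditions, CESD-10 and site.
- For each variable in turn, add the variable and its product with group to the T2 ANCOVA. Keep age, number of conditions and CESD-10 continuous.
- Report each interaction estimate with its 95% CI, label the analyses exploratory, and claim no subgroup-specific effectiveness from a within-subgroup p-value.
- Remove dose from the baseline subgroup variables and give the reason: it is defined over the six-month intervention and exists only in the CAST arm. Report it descriptively as an implementation outcome, as Table 2 already provides.
- Reconcile the subgroup paragraph (baseline to T2) with Table 1 (also T2-T3), so that both name the same periods.

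The cost is a few sentences and a few model terms. The downside is low power: about 30% to 37% for a 6.5-point difference in effect between halves (r = 0 to 0.5). A non-significant interaction is therefore weak evidence of a uniform effect, and the interval should carry the interpretation.

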### Randomization and blinding

Within each study region, participants will be assigned to either the intervention or the usual care group following the collection of baseline data, using stratified permuted block randomization administered by a centralized web-based service (RedCap) to allocate clients at each site to the two groups in accordance with the sequence and using a 1:1 ratio. All study participants will be blinded to their group allocation (usual care or CAST intervention). Research assistants completing further assessments with participants following recruitment will remain blind to group assignments for the duration of data collection. Upon completion of the study at 12-months, participants will receive a mailed debriefing letter describing the two groups and their group allocation.

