This pragmatic trial is a tailored intervention with fixed and flexible elements that are adaptable to patient needs and preferences and the local context. Consistent with a pragmatic trial, participants allocated to the CAST intervention, can accept or decline as much of the intervention as they want. Examples of allowable adaptations include removing and/or integrating elements that overlap with routine or usual care. The CTCs will attend an 8-h training session supported by role-appropriate and standardized manuals. Training sessions will be led by the Principal Investigators and the Research Coordinator and include education and role-playing to enhance skills in problem-solving therapy within the context of MCCs.

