#### Usual care group

Participants allocated to the control group at discharge from hospital to home will receive usual care. Usual care, which varies from site to site, may include recommendations for the patient to see their primary care provider and/or other medical specialists or access home care and/or other health and social services provided in the community after hospital discharge.

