#### Implementation measures and data sources

##### Implementation outcomes

Five implementation outcomes will be examined as part of this study: i) adoption or uptake refers to the engagement rate and the dose of the intervention by research participants defined as the number of home visits and telephone contacts during the six-month intervention; ii) acceptance refers to the acceptability of the intervention by study participants assessed using semi-structured interviews with participants; iii) feasibility refers to the ability to recruit participants who meet the eligibility criteria, and the feasibility of delivering the intervention in the local setting; and iv) fidelity is the extent to which the intervention was implemented as intended (see Table 2). Reasons for discontinuing the intervention will be recorded. The interview guide for the older adult and caregiver participants receiving the CAST intervention is provided as supplementary data (see Additional file 3).

**Table 2 Tab2:** CAST Study Implementation Evaluation Summary

Question/Focus	Definition/Data Source	Method of Analysis
Implementation outcomes [66] a) Adoption (uptake) b) Acceptability c) Feasibility d) Fidelity	a) Engagement rate b) Post-intervention interviews; care transition coordinator direct and indirect activities c) Recruitment rate d) Fidelity checklist)	a) Proportion of participants who agreed to at least one CTC visit among those in the intervention group Calculate the dose of the intervention, defined as the number of CTC home visits and telephone contacts during the six-month intervention b) Qualitative content analysis c) Proportion of eligible individuals who enrolled in the study d) Mean number of times each core component of the intervention was implemented
Implementation and adaptation of CAST intervention	• Notes from meetings with sites • Research team meeting notes • Research coordinator notes • Care transition Coordinator interviews • Notes from CAB meetings and focus groups	The Consolidated Framework for Implementation Research (CFIR) [65, 67] is being used to guide the development of interview guides and will serve as a framework for data coding and analysis. Content analysis [68] will be conducted using primarily deductive approach.

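### Intervention dose is listed as a baseline subgroup variable, but it arises after randomisation and only in the CAST arm, so the subgroup test is either inestimable or non-randomised

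*Protocol article*

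**What the plan says.** All references are to the protocol article.

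- **Subgroup plan** (Analysis: effectiveness evaluation). The purpose is stated as "Subgroup analyses will be conducted for the VR-12 outcomes to determine if the intervention is effective for subgroups of patients from baseline to T2". The variables are introduced with "The following baseline variables have been selected a priori for testing subgroup effects". They are age, sex, number of chronic conditions, and then "depressive symptoms (CESD-10), site, and dose of the intervention (number of home visits and telephone contacts".
- **Definition of dose** (Implementation outcomes). Dose is "defined as the number of home visits and telephone contacts during the six-month intervention". Table 2 specifies whose contacts count: "Calculate the dose of the intervention, defined as the number of CTC home visits and telephone contacts during the six-month intervention".
- **Timing of allocation** (Randomization and blinding). "participants will be assigned to either the intervention or the usual care group following the collection of baseline data".
- **Control arm** (Usual care group). "Participants allocated to the control group at discharge from hospital to home will receive usual care". No Care Transition Coordinator (CTC) contact is described for this arm.
- **What determines dose.** Under CAST intervention group, "participants allocated to the CAST intervention, can accept or decline as much of the intervention as they want". The same section schedules contacts around needs and preferences, above a minimum of two visits and four calls. The Discussion expects dose to vary with individual need.

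**The concern.** A subgroup analysis of a randomised trial keeps its protection from confounding because the subgroup is fixed before allocation, so each subgroup holds comparable treated and control participants. Five of the six listed variables meet that condition: age, sex, number of chronic conditions, CESD-10 and site. Dose does not. It accrues over the same six months as the outcome, it is shaped by what participants want and need, and it has no counterpart in usual care.

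At stake is the reading of a secondary analysis of the VR-12 scores, which include the primary outcome, the MCS. Reported under the labels of baseline and pre-selected, a dose result would carry the standing of a randomised subgroup finding. In fact it would be an observational comparison that can show an effect when there is none.

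**Working it through.** **1. Does dose exist at baseline?** Baseline data come first, then allocation, then six months in which CTC contacts are counted. At baseline no participant has a dose. The subgroup section therefore contradicts the article's own definition of dose, and no other section resolves this.

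**2. Can a treatment-by-dose interaction be estimated?** Let G = 1 for CAST and 0 for usual care, and let D be dose. Every control has D = 0, so G × D = D for every participant. The design matrix with columns 1, G, D and G × D has two identical columns. A numerical check with 86 per arm gave rank 3 of 4. The interaction has no separate estimate.

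**3. Numbers for an illustration.** The Sample size section gives 216 in total, 20% attrition, SD 15.0, difference 6.5, alpha 0.05 and power 80%. Its figure reproduces closely:
- Normal approximation, two-sided: n per arm = 2 × (1.96 + 0.8416)² × 15² / 6.5² = 83.6, rounded up to 84. The total is 168, and 168 / 0.80 = 210.
- t-test version: 85 per arm, and 170 / 0.80 = 212.5, so 213.
- Stated: 216, within 3% of 210.

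The number analysed is 216 × 0.80 / 2 = 86.4, so 86 per arm. A median split of CAST gives 43 per dose half.

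**4. Size of the bias when the true effect is zero.** Let r be the correlation between dose and the part of the MCS outcome that treatment does not explain. The documents give no value for r, so it is an assumption. For a median split of a normal variable, the mean of the upper half is √(2/π) = 0.80 SD above the overall mean. Hence:

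- Apparent effect, above-median half against all controls = 0.80 × r × 15
- Standard error = 15 × √(1/43 + 1/86) = 2.80

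| Assumed r | Apparent effect (MCS points) | False-positive rate, nominal 5% |
|---|---|---|
| 0 | 0 | 5% |
| 0.1 | 1.2 | 7% |
| 0.2 | 2.4 | about 13% |
| 0.3 | 3.6 | about 25% |
| 0.4 | 4.8 | about 40% |

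A simulation of 4,000 replicates with the same inputs gave 1.2, 2.3, 3.5 and 4.7 points and 7%, 13%, 24% and 40% for r = 0.1 to 0.4.

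**5. With baseline adjustment, as in the planned ANCOVA.** Assume a baseline-outcome correlation of 0.5. The residual SD is 15 × √0.75 = 13.0. At r = 0.4 the apparent effect is 0.80 × 0.4 × 13.0 = 4.2 points. The rejection rates do not change, because bias and standard error shrink together. A second simulation with this adjustment gave about +2.0 and −2.1 points in the high and low halves at r = 0.2, and +3.0 and −3.1 at r = 0.3. Testing the high half against the low half rejected in 31% and 60% of replicates. At r = 0 it rejected in 5%.

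**6. Sign.** If participants with a better outlook accept more contacts, r is positive and high dose looks beneficial. If sicker participants receive more contacts, r is negative and every apparent effect above changes sign.

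**The case against.** **The article specifies no interaction model.** A within-CAST dose-response analysis can be fitted, and an unseen analysis plan might choose one. This is fair: non-estimability applies to a treatment-by-dose interaction, not to every use of dose. However, the stated purpose is to learn whether the intervention is effective within subgroups, which needs controls in each subgroup. A within-CAST analysis cannot answer that and is not randomised. Nor is this detail left to a later plan, because the article states the classification of dose as baseline and states it wrongly.

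**The size is assumed.** This stands. With r = 0 there is no bias, and the figures are an illustration, not a forecast.

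**The direction is not known.** A reader might infer that high-dose participants will look falsely improved. The documents do not support one sign, because they tie contacts to need as well as to choice. It is also tempting to say that death, readmission or withdrawal lowers the count. That is plausible but not stated, and readmission could equally prompt more contacts.

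**The consequence is limited.** A reader might infer that a spurious dose result would pass straight into decisions on how much of the intervention to scale up. The documents do not say so. The scale-up strand rests on qualitative content analysis of notes, interviews, focus groups and a Citizen Panel, and the implementation evaluation summarises dose descriptively.

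**Conclusion.** The point holds as a stated error of moderate severity. Dose is called a baseline variable, although the article's own definition places it after randomisation and in one arm only. A treatment-by-dose interaction is inestimable. The available alternatives, CAST dose strata against all controls or against each other, are non-randomised and biased whenever dose relates to prognosis. The article makes that likely by letting choice and need determine dose.

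For the comparison with all controls, assuming no true effect, SD 15, 86 per arm and a median split, the bias runs from 0 at r = 0 to about 4 to 5 MCS points in either direction at |r| = 0.4. The false-positive rate runs from 5% to about 40%. For scale, the design difference is 6.5 points. The values of r are assumptions.

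A reader might take this as a threat to the main result. It is not: the primary intention-to-treat ANCOVA uses group and baseline value only, the sample size does not depend on dose, and the other five subgroup variables are sound in this respect.

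**What to change.** Delete dose from the list of baseline subgroup variables, leaving age, sex, number of chronic conditions, CESD-10 and site. Keep dose as the descriptive adoption outcome already planned under Implementation outcomes and under Quantitative data in the implementation analysis. If a dose-response analysis within the CAST arm is wanted, label it exploratory and non-randomised.

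A complier-average analysis, with randomisation as the instrument, is optional. Its exclusion restriction requires that allocation to CAST has no effect on people classed as non-receivers. Setting receipt at the full minimum of two visits and four calls strains this, because the article expects partial receipt and those below the threshold may still benefit. A lower threshold, such as the at-least-one-visit criterion behind the engagement rate in Table 2, is easier to defend. Even then, participants with telephone contact only could benefit, so the assumption should be stated.

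The cost is a one-sentence change. The sample size stays at 216. What is lost is a naive dose subgroup result.
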